Although previous research suggests that a negative attentional bias is associated with the use of less effective emotion regulation strategies [26, 42] and hence lower mood recovery from stress [22], research has not tested the causal effects of modifying attentional bias on stress responses in depressed samples, yet. Whereas ABM effects on symptoms are assumed to manifest themselves over a longer period of time (see for instance, [23, 33]), effects on mood reactivity and recovery from stress should be visible shortly after the training already. Hence, the present study also includes a stressful speech task at post-assessment, as a more sensitive measure of the potential therapeutic effects. In line with findings of Sanchez and colleagues [22], it is hypothesized that the PT group shows a higher mood recovery from the stressor than the ST group. Moreover, effects on general levels of resilience over time are measured.

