### Primary outcome measures

The main outcome measures are change in attentional bias, change in depressive symptomatology and mood response and recovery from stress.

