#### Mood reactivity and recovery from stress

To investigate training effects on mood changes in response to a stressor, an adapted version of a speech task as used by Sanchez et al. [22] is used. At the beginning of this task, participants sit in front of a black computer screen and rest for a period of five minutes. Afterwards, they rate their mood, and are then informed by means of computer instructions, that they will get two minutes to prepare a five-minute-speech on the topic – e.g., “Why am I a good friend?”. This topic has effectively induced stress levels in patients with MDD in the study of Sanchez and colleagues. Participants are told that the speech will be video recorded and evaluated on its quality by two independent researchers. However, they are also informed that not everybody would have to give the speech eventually. Instead, the computer would randomly choose, who actually has to give the speech. During the following two-minutes of preparation, participants are allowed to take notes with pen and paper and, to increase the stress level, a clock on the computer-screen signals the time left. After preparation, participants again rate their current mood before the computer informs them, that they would not have to give the speech. They are then given another five minutes to rest and rate their mood for a last time afterwards. This procedure has successfully been used by Sanchez and colleagues to investigate the relation between attention bias and stress responses in depressed individuals.

Mood changes during the speech task are measured by means of a six-item, state version of the Spielberger State-Trait Anxiety Inventory (STAI; [56, 57]) and a state version of the international short form of the Positive and Negative Affect Schedule (I-PANAS-SF; [58]). The STAI-S contains six items related to anxiety (i.e., calm, tense, upset, relaxed, content, worried) that are rated on a 4-point scale (1 = *not at all* to 4 = *very much*). This short form of the STAI has been proven sensitive to fluctuations in state anxiety and shows comparable psychometric properties as the full-form [56]. The I PANAS-SF contains five items related to positive and five items related to negative affect, rated on a five-point scale (1 = *very slightly* or *not at all* to 5 = *extremely*) and has shown to be psychometrically acceptable [58].

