### Analyses

#### Sample size

Wells and Beevers [29] reported a large effect of ABM on change in bias (*η*
^*2*^ = .16) and on depressive symptoms (*η*
^*2*^ = .32). Likewise, Beevers et al. [35] observed a large effect for change in bias from pre- to post-ABM within the training condition (*d* = 1.01, *η*
^*2*^ = .20), but not the control condition (*d* = .04, *η*
^*2*^ = .0004). However, the above-mentioned studies were conducted in a sample of dysphoric students [29] and in a sample of treatment-seeking current MDD patients, some of whom received pharmacological treatment [35]. In the present study, ABM is provided during the waiting period for psychotherapy or in combination with pharmacological treatment and/or psychotherapy (i.e., IPT, CBT, psychiatric care). In order to account for the greater heterogeneity of our sample and because recent meta-analyses of the effects of CBM in anxiety and depression suggest rather small effects [28, 41], we conservatively assume a small to medium effect size of *η*
^*2*^ = .02 (i.e., *f* = .142). A-priori sample size is calculated with G*Power for F-tests for repeated-measures (RM) Analysis of Variance (ANOVA) with within-between interaction effects and an effect size specification as recommended by Cohen [83]. To be able to detect this effect size over two time-points, with an α-level of .05 and a power-level of .80, a total sample size of 100 would be needed, thus 50 participants per group. Compensating for an expected attrition of 20 %, we need to include 50/0.80 = 62.5, thus 63 participants per condition and *N* = 126 in total.

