### Analysis plan

#### Clinical evaluation

In accordance with the Consolidated Standards of Reporting Trials (CONSORT; [84]), all analyses of the primary and secondary outcome parameters will be carried out in accordance with the intention-to-treat (ITT) principle. Missing values due to drop-out will be imputed (e.g., by using multiple imputation (MI) or expectation maximization (EM)). Additional sensitivity analyses will be conducted to gauge the robustness of the findings, by including and excluding these participants in the analysis.

ABM effects on the primary outcome measures, attentional bias and depressive symptoms, will be tested by means of RM ANOVAs, with condition (PT, ST) as between-subjects factor and time (pre-test, post-test) as within-subjects factor. Likewise, training effects on stress responses will be investigated with a 2 (condition: PT, ST) × 3 (time: before stress, anticipatory stress, stress recovery) RM ANOVA with I PANAS-SF and STAI-S scores as dependent variables. All analyses will be conducted with and without covariates, in case variables are unevenly distributed across groups (e.g., bias or depression at baseline, number of previous depressive episodes, or number of completed training sessions), to test the robustness of the results. To investigate long-term effects of ABM on depressive symptoms, the analysis of this primary outcome parameter will be repeated over five time points (baseline, post-test, one, six, and 12 months follow-up).

Effects on secondary outcome measures will be analyzed by means of ANOVAs or ANCOVAs over two time points (baseline, post-test) in case of the cognitive transfer measures, and over four time points (baseline, post-test, one and six months follow-up), in case of rumination, positive and negative affect, and resilience.

Exploratory analyses will be directed at the process measures and will additionally be performed to take the role of potential moderators into account, such as timing of the training (i.e., during waiting period vs. next to UC) type of UC (IPT, CBT, psychiatric care), or to predict training effects based on other disorder-related characteristics assessed during baseline.

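### The stated hypothesis is about mood recovery from the stressor, but the only named test is a 2 × 3 interaction that mixes recovery with reactivity

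*Protocol article*

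**What the plan says.** The Aim and hypotheses section makes one directional prediction for the speech task: "it is hypothesized that the PT group shows a higher mood recovery from the stressor than the ST group". The sentence leading up to it is wider and says that "effects on mood reactivity and recovery from stress should be visible shortly after the training already".

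The Primary outcome measures section also lists the wider outcome: "The main outcome measures are change in attentional bias, change in depressive symptomatology and mood response and recovery from stress".

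The section on mood reactivity and recovery from stress describes three mood ratings: after an initial rest, after two minutes of speech preparation, and after a second rest ("They are then given another five minutes to rest and rate their mood for a last time afterwards"). I call them R1, R2 and R3, because T1 to T5 denote the study visits.

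The Clinical evaluation section names one test: "training effects on stress responses will be investigated with a 2 (condition: PT, ST) × 3 (time: before stress, anticipatory stress, stress recovery"), specified as an "RM ANOVA with I PANAS-SF and STAI-S scores as dependent variables". The article states no recovery score, no contrast between ratings, and no rule linking the ANOVA result to the recovery hypothesis.

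**The concern.** Recovery concerns one segment of the task, from the stress rating to the final rating. The 2 × 3 interaction concerns all three ratings together. Its null hypothesis is that the PT-minus-ST difference is the same at R1, R2 and R3, which is a different null from equal recovery. The interaction can be significant because PT blunts the rise during preparation while both arms then come down by the same amount.

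This is a primary outcome, and the rationale is specifically about recovery: the article builds on a finding that slow disengagement from negative material predicts poorer mood recovery. If the interaction is the only result fixed in advance, the trial cannot say from that result whether its recovery hypothesis was supported. Any contrast chosen afterwards would be chosen with the profiles in view.

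**Working it through.** **The plan's own figure.** The Sample size section takes η² = .02 over two time points, "with an α-level of .05 and a power-level of .80", and arrives at N = 100. f² = .02/.98 = .0204. With λ = f²·N·m/(1 − ρ), m = 2 time points and an assumed ρ = .5 (the article gives none), λ = .0204 × 100 × 2/.5 = 8.16 on 1 and 98 df, and power is .808. So 100 reproduces under that parameterisation, and 50/0.80 = 62.5 gives 63 per arm. The calculation is for two time points, not for the three-rating stress test. I use it only for the analysed number, 50 per arm.

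**Inputs.** From the article: n = 50 per arm, α = .05, two arms, three ratings. My assumptions: SD 1 at each rating, compound symmetry with ρ = .3, .5 or .7, and a group difference of 0.5 SD. Lower scores mean better mood, as on the STAI-S and the negative-affect items; signs reverse for positive affect.

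**Formulas.** Let d = (d1, d2, d3) be the PT − ST mean differences at R1, R2 and R3.
- Interaction: λ = (n/2)·Σ(dj − d̄)²/(1 − ρ), on 2 and 196 df.
- Recovery contrast, R3 − R2: noncentrality δ = (d3 − d2)/√[2(1 − ρ)·2/n], on 98 df.

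**Reactivity differs, recovery equal: d = (0, −.5, −.5).** d̄ = −1/3, and the squared deviations are 1/9 + 1/36 + 1/36 = 1/6. So λ = 25 × (1/6)/(1 − ρ).

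| ρ | λ | interaction rejects | R3 − R2 contrast rejects |
|---|---|---|---|
| .3 | 5.95 | 57.3% | 5.0% |
| .5 | 8.33 | 72.9% | 5.0% |
| .7 | 13.89 | 92.2% | 5.0% |

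A simulation of 10,000 trials at ρ = .5 agrees: 72.6% for the interaction and 5.1% for the contrast (5.4% for the interaction when nothing differs). In 36.8 of those 72.6 points, about half, the R3 − R2 estimate does not favour PT.

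**Sensitivity.** With 63 per arm the three interaction rates are 68%, 83% and 97%. With a 0.3 SD difference and 50 per arm they are 24%, 32% and 50%.

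**Other profiles.** The sum of squared deviations is also 1/6 for a difference at the peak only, (0, −.5, 0), for more recovery under PT, (0, 0, −.5), and for less recovery, (0, 0, +.5). The interaction therefore has the same rejection rate in all four cases and cannot tell them apart.

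**Price of a contrast when only recovery differs: d = (0, 0, −.5).** At ρ = .5, |δ| = .5/√(2 × .5 × 2/50) = .5/.2 = 2.5, giving power 69.7% against 72.9% for the interaction. At ρ = .3 it is 55.3% against 57.3%, and at ρ = .7 it is 89.2% against 92.2%. The loss is 2 to 3 points; a simulation over ρ = .5 to .8 put it at no more than about 4.

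**The definition of recovery matters.** In the peak-only case at ρ = .5, R3 − R2 goes significantly against PT in 69.7% of trials, while R3 − R1 rejects at only 5.0%. Two reasonable definitions can disagree on the same data.

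**The case against.** The strongest reply is that the ANOVA matches the outcome as listed. The abstract, the Primary outcome measures section, Table 1 and the heading of the speech-task section all name mood response or reactivity, most of them together with recovery, and the ANOVA is introduced as a test of stress responses. For that wider outcome, a pure reactivity difference is a real effect, and the percentages above are power, not error. This stands: the ANOVA is not the wrong test for stress response, and it should not be replaced.

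A reader might infer more: that the test is specially defective because it can reject when PT recovers less. The documents and the arithmetic do not support that. Any two-sided test can reject in the wrong direction; the 1-df contrast does so in 69.7% of trials in the less-recovery case at ρ = .5, against 72.9% for the interaction. The difference is that a 1-df contrast has a sign that settles the direction, whereas a 2-df interaction has none.

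Nor does the article say that a significant interaction will be counted as proof of better recovery, and follow-up contrasts may be in an analysis plan that is not shown. That limits confidence. It does not remove the mismatch between the one hypothesis stated and the one test named. The linear mixed model mentioned as an alternative would not help, since three-level time gives the same 2-df interaction.

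Finally, scoring R3 − R2 as recovery is a choice that the article does not make. Under it, an arm with a blunted peak and the same end point looks worse only because it had less to recover from. This also stands, and it shapes the fix.

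**Conclusion.** The point holds in limited form. The 2 × 3 interaction is a sound overall test of stress response but cannot by itself support the stated recovery hypothesis. The mismatch follows from the 2-df null and does not depend on any assumed number. Its size does: the 57%, 73% and 92% figures rest on 50 per arm, equal SDs, compound symmetry, a 0.5 SD reactivity difference and R3 − R2 as the measure of recovery. The article gives no SD, correlation or expected effect for the speech task, so the figures illustrate what can happen and do not estimate how likely it is. Confidence is moderate. The change is worth making because it decides what the trial can conclude on a primary hypothesis.

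**What to change.** In the Clinical evaluation section, keep the 2 × 3 ANOVA as the overall test of stress response and add two planned 1-df between-arm contrasts for each mood scale, each with an estimate, a 95% CI and its direction:

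- **Recovery**, with the definition fixed before unblinding: for example the stress-recovery rating minus the anticipatory-stress rating, or the stress-recovery rating adjusted for the two earlier ratings.
- **Reactivity**: the anticipatory-stress rating minus the before-stress rating.

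State that better recovery will be claimed only if the recovery contrast favours PT, and that it will be read together with the reactivity contrast, because a lower peak leaves less to recover from.

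The cost is a sentence or two in the plan and no new data. The recovery claim would rest on a test with slightly less power than the interaction when only recovery differs, and a reactivity-only effect would no longer count as confirming the recovery hypothesis.

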#### Randomization and blinding

Participants are randomly allocated to one of the two groups, right before the first training session. Randomization is computerized and stratified for depression severity (<39 = moderate; 39–48 = severe; > 48 = very severe) at baseline, as assessed by the Inventory of Depressive Symptomatology self-report (IDS-SR; [52]), as well as for age (18–35 years; 36–50 years; 51–65 years). In case participants indicate, that they want to discontinue with the study and withdraw consent for using their data, intervention allocation is corrected for the excluded participants.

Based on the IDS-SR score and age, the computer generates a random 5-digit number, which is linked to one of the two training conditions and which further identifies participants and their documents. This blinding code is managed by an independent statistician and revealed to researchers only, after all participants have completed the last assessment. Hence, both participants and researchers are blind to the training conditions.

To assess if participants remained blinded to their group allocation, all participants fill in an awareness check at post-test, investigating which training condition (PT or ST) they believe they have been enrolled to.

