#### Process measures

Training task performance is assessed for both the PT group and the ST group by comparing average RTs for incompatible trials (in the PT: catch trials) to average RTs for compatible trials across training blocks and sessions. Based on this, learning curves within each session and losses of training effects between sessions will be investigated. To evaluate effects of the online training sessions on mood, three visual analogues scales (VAS) are administered prior to and following each dot-probe session. The VAS scales were adopted from Sanchez et al. [22] and consist of three items each: happy mood (happy, optimistic, joyful), anxious mood (nervous, tense, anxious), and sad mood (depressed, upset, sad). Participants are asked to indicate their current mood on a line with anchor points ranging from 0 (*not at all*) to 10 (*very much*).

To control for possible placebo effects of the intervention, the Credibility/Expectancy Questionnaire (CEQ; [77]) is used. The CEQ is a short self-report questionnaire that measures how credible and convincing the patient experiences the intervention and what the patient expects from it. The questionnaire in this study has been adapted from a Dutch version of this questionnaire for chronic back pain patients [78]. It comprises three questions regarding the credibility of the intervention and three questions assessing participants expectations, all of which are answered on a 9-point scale (1 = *not at all* to 9 = *very much*).

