During the first training session (session 2), participants receive written and verbal practical information regarding the online training-program. They then complete the first training which is, like all dot-probe trainings, flanked by brief mood state measures (VAS). Afterwards, the CEQ is administered and appointments are made for the seven training sessions (session 3–9), as well as for the post-assessment (session 10). The eight training sessions are distributed across two weeks, with four weekly sessions. During the two weeks of training, participants receive automated e-mails reminding them of the planned sessions. In case, participants do not complete the planned sessions, even though they have been reminded by e-mails, they are given a call by the experimenter who asks them to still complete the session. The post-assessment, which again takes place at Pro Persona, is scheduled at least one week and a maximum of two weeks after the last training session. The post-assessment is comparable to the baseline assessment but without the Tic-P and the RS, and with the additional speech task. Afterwards, appointments are made for the subsequent follow-up assessments and participants receive a reimbursement for their travel cost (15 Euros).

During the first two follow-up assessments (session 11 & 12), participants complete questionnaires via the internet (IDS-SR, STAI-T, RRS, RS, PANAS, EQ-5D-3 L). At 12 months follow-up (session 13), the MINI is administered via telephone to assess the diagnostic status of depression. Moreover, participants complete the IDS-SR, EQ-5D and Tic-P via internet. After having filled in the questionnaires, participants receive a debriefing form with contact information of the coordinating investigator, who can be contacted in case of questions. The use of medication as well as the number of psychological treatment sessions is monitored at the post-test and all follow-up measures. For an overview of all measures and corresponding time points, see Table 1.

**Table 1 Tab1:** Overview of all measures and corresponding time points

Domain	Target Concept (Measure)	T0	T1	Training 1	Training 2–8	T2	T3	T4	T5
Screening measures	Inclusion Criteria Interview	•							
	Diagnostic status (MINI)	•							•
Primary outcome measures	Attentional Bias (Dot-probe)		•			•			
	Depressive Symptomatology (IDS-SR)		•			•	•	•	•
	Mood response and recovery from speech task (I PANAS-SF & short STAI-S)					•			

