Finally, mediation analysis will be conducted to investigate whether change in attentional bias across sessions mediates the relationship between training condition and depressive symptoms. A second exploratory mediation analysis will test the mediating effect of rumination. This analysis will only include participants who completed an adequate dose of training sessions (i.e., 6–8).

As alternative to general linear models (GLM), which have been the standard approach to analyzing data of similar trials as the one proposed, more recent statistical developments including linear mixed models (LMM) might be considered when analyzing the data.

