Next to the long-term effects on clinical symptoms of depression, the present study further aims at extending findings of previous studies, by investigating whether the training affects emotion regulation in response to stress and general levels of resilience. Regarding the mechanisms of symptom change, it is assumed that effects on symptoms manifest themselves over a longer period of time, after the bias has been repetitively deployed in stressful daily life situations [17, 40]. Although there is evidence that the prolonged processing of negative information is related to impaired mood recovery after stress [22], this is the first study examining the causal link between attentional bias and stress responses in depression.

Moreover a range of exploratory questions are addressed. To get more insight into mechanisms associated with symptom change, we additionally test the mediating role of rumination in ABM effects. Second, transference effects to attentional bias for verbal materials and to other cognitive measures, including cognitive control and prospective positive mental imagery are investigated. Third, the credibility of the training and related expectancies are measured and controlled for. The latter will not only provide insight into the role of placebo effects within ABM research, but may also give an indication of the acceptance of such a computerized training among patients.

Altogether, this study will enhance our understanding regarding the role of attentional bias in depression and the potential therapeutic effectiveness of ABM in this population. To our knowledge, this is the first study testing the cost-effectiveness of an ABM training in clinically depressed patients in a specialized mental health care setting. It thereby also provides insight into the combination of UC and ABM and whether adding such an internet-based intervention, requiring limited to no time of experienced clinicians, is indeed economically sensible. If the training shows the expected beneficial effects, this study will form an important step towards the implementation of ABM in clinical practice and the optimization of UC through computerized self-help trainings.

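### The robustness covariates include the number of training sessions completed, a post-randomisation variable that can bias the adjusted arm comparison

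*Protocol article*

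**What the plan says.** All references are to the protocol article.

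- **Analysis plan, Clinical evaluation.** Primary and secondary outcomes are analysed by intention to treat. Then: "All analyses will be conducted with and without covariates, in case variables are unevenly distributed across groups". The bracketed examples are baseline bias, baseline depression and "number of previous depressive episodes, or number of completed training sessions), to test the robustness of the results".
- **Randomization and blinding.** "Participants are randomly allocated to one of the two groups, right before the first training session".
- **Clinical evaluation, mediation.** One mediation analysis concerns change in attentional bias. A second, exploratory one concerns rumination and is followed by: "This analysis will only include participants who completed an adequate dose of training sessions (i.e., 6–8" of the eight sessions).

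**The concern.** An uneven baseline variable in a randomised trial is a chance event, and adjusting for it is harmless or helpful. Session count is different. It accrues after allocation, so a difference between arms may be a consequence of the training received. The two trainings differ in how often the probe replaces the positive picture, and seven of the eight sessions are done at home.

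If the same unmeasured factor (motivation, say) raises both sessions completed and improvement, participants with equal session counts are no longer comparable across arms. Those in the arm with fewer sessions will on average have more of that factor. The adjusted contrast then shows an arm difference even when there is none.

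The imbalance trigger does not separate the two situations: it brings the covariate in whenever the arms differ on it, whether by chance or because of the training. Because the result is labelled a robustness test, disagreement with the unadjusted analysis would be read as fragility, and agreement as support. Neither reading would be warranted.

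Restricting the rumination mediation to participants with 6 to 8 sessions conditions on the same variable by selection.

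**Working it through.** **1. Sample size used.** From the Sample size section: η² = .02, α = .05, power .80, two time points, 100 evaluable, 20% attrition.

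- f = √(.02/.98) = .143 (the article gives .142).
- λ = f²·N·m/(1−ρ). With N = 100, m = 2 and ρ = 0.5 (not stated, so assumed), λ = .0204 × 100 × 2 / 0.5 = 8.16 and power is .808. The 100 reproduces.
- 50/0.80 = 62.5, so 63 per arm and 126 in total, as stated.
- For scale, λ = N·d²/4 gives d = √(4 × 8.16/100) = 0.57 SD of change.

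**2. Timing.** Allocation precedes session 1, so no participant has a session count before allocation. Baseline bias, baseline depression and previous episodes all precede it.

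**3. Expected bias.** Let A be arm and U an unmeasured prognostic factor. Let latent session completion be S = a·A + b·U + noise and outcome change be Y = c·U + noise, with U and both noise-plus-U parts at unit variance and no effect of A on Y. The slope of Y on S within arm is b·c, so adjusting for S shifts the arm coefficient by −a·b·c. This is zero if a = 0, b = 0 or c = 0.

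- a = −.3, b = c = .5: .3 × .5 × .5 = 0.075
- a = −.5, b = c = .5: .5 × .5 × .5 = 0.125
- a = −.5, b = c = .7: .5 × .7 × .7 = 0.245

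**4. Simulation.** Same model, with sessions rounded and limited to 0–8 (centre 6.5, SD 2 before limiting). There were 63 per arm, a true effect of zero and 4000 runs per row. Monte Carlo error at 5% is √(.05 × .95/4000), about 0.3 percentage points. All values of a, b and c are assumptions.

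| Arm shift in sessions (SD) | Correlation of U with sessions / with change | Unadjusted: bias, rejection | Adjusted for sessions: bias, rejection |
|---|---|---|---|
| 0 | .5 / .5 | 0.00, 4.8% | 0.00, 5.1% |
| −.5 | 0 / .5 | 0.00, 4.8% | 0.00, 4.6% |
| −.3 | .5 / .5 | 0.00, 5.0% | 0.07, 7.4% |
| −.5 | .5 / .5 | 0.00, 5.1% | 0.11, 9.5% |
| −.5 | .7 / .7 | 0.00, 4.8% | 0.23, 28.3% |

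Rounding and the ceiling at 8 make the bias slightly smaller than in step 3. Against the 0.57 SD of step 1, 0.07 is about 12% and 0.23 about 40%. With 50 per arm the last three rows give 0.07 (6.0%), 0.11 (8.2%) and 0.22 (22.7%).

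**5. Effect of the trigger.** Keeping only runs with a significant session imbalance (one reading of uneven distribution), the adjusted results in the last three rows are 0.07 (7.7%), 0.11 (9.1%) and 0.23 (28.1%).

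**6. Selection on 6 to 8 sessions.** In the last three rows, an arm contrast among those with at least 6 sessions has bias 0.04, 0.07 and 0.15 SD, with rejection of 5.8%, 5.9% and 9.5%. This only indicates the mechanism. It is not the mediation estimate.

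**The case against.** Several points on the other side stand.

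- **The main result is untouched.** The unadjusted analysis is always produced, and nothing lets the adjusted one replace it. A reader might infer that the plan contradicts its own intention-to-treat commitment. It does not: adjustment excludes and reassigns no one, and that commitment covers primary and secondary outcomes, not an exploratory mediation.
- **Bias needs two conditions.** Arm must move session count, and a shared cause must drive change. The attentional bias and depression analyses are condition-by-time tests, so a factor that shifts pre and post equally cancels out. A separate check of that case gave bias of about 0 and type I error of 4.5% to 5.4%. Trial numbers are equal in the two arms, participants and researchers are blinded, and reminders are not described as arm-specific, so the documents give no reason to expect a large arm-caused difference.
- **Under pure chance imbalance, adjustment helps.** In the first row of the table, among runs with a significant session imbalance, the unadjusted test rejected in 9.7% and the adjusted test in 5.1%. The data cannot show whether an observed imbalance is chance or caused by arm, however, so this does not justify the covariate.
- **The mediation restriction is narrow.** Its singular wording follows the rumination analysis and most naturally covers that alone.

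A reader might also infer that expectancy is a second post-randomisation covariate. The questionnaire follows the first training session ("Afterwards, the CEQ is administered and appointments are made for the seven training sessions"), and the Discussion says "the credibility of the training and related expectancies are measured and controlled for". But no passage enters it in an effect model. Aim and hypotheses gives its purpose as showing equal expectations in both arms. The questionnaire is listed under Process measures, which the analysis plan treats as exploratory. The documents do not support that reading.

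**Conclusion.** The point holds in limited form. The plan names a post-randomisation variable as a covariate in a robustness check and brings it in when the arms differ on it. That check can mislead about the unadjusted result but does not bias it.

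Bias of about 0.07 to 0.23 SD and type I error of about 7% to 28% illustrate a possible harm. They depend on an arm shift of 0.3 to 0.5 SD in sessions and a factor correlated .5 to .7 with both sessions and outcome change, none of which the documents give. The 28% is the extreme of that range, and the bias is nil if either condition fails. The simulation uses a single change outcome, so it does not reproduce the five-time-point or stress-task analyses.

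The article states the covariate itself, so this is not a detail left to a separate analysis plan. It should be fixed, though the trial's main conclusion does not depend on it.

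**What to change.** - In Clinical evaluation, delete sessions completed from the example covariates. Limit the robustness covariates to variables measured before randomisation, and fix the list before the allocation code is released. Session counts can still be reported descriptively by arm.
- Run the exploratory rumination mediation in all randomised participants. Keep the 6 to 8 session subset as a sensitivity analysis, labelled as a non-randomised comparison.

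The cost is analysis wording only. The sample size of 126 and the data collected do not change. The one downside is that low-dose participants will somewhat dilute the full-sample mediation estimate.
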